## Abstract

**Background:**

Despite tremendous investment worldwide, hypertension treatment and control rates remain low. The complexity and long-term dynamics of influencing factors make personalized management inevitable and challenging. This protocol describes Personalized Hypertension Management in Anhui, China (PHMA), a project that uses a package of innovative approaches in tailoring interventions to individual patient’s dynamic complications and contexts.

**Methods/design:**

PHMA strives to reduce hypertension harms by eight “objective behaviors” (e.g., self-monitoring and reporting, healthy diet, physical exercise/activities). These objective behaviors are promoted through five intervention measures: support for self- monitoring, supervised machine communications, daily education or reminder messages, weekly blood pressure notification, and quarterly signed feedback. PHMA uses ten categories and over 300 variables in selecting and refining intervention procedures and content for individual patients. Efficacy of the intervention package is evaluated using a cluster randomized controlled trial design involving a total of 60 site communities and 3352 hypertension patients. Primary measure for the evaluation is systolic and diastolic blood pressure; while secondary evaluation measures include quality of life (EQ5D-5L), occurrence of hypertension-related complications (such as cerebral hemorrhage, coronary heart disease, myocardial or cerebral infarction), healthcare utilization and scores of objective behaviors.

**Discussion:**

PHMA uses novel, low cost and sustainable approaches to tailor interventions to the dynamic conditions and contexts of individual patients. Unlike contemporary approaches to hypertension management which are mainly population based, each participant patient in PHMA applies a unique intervention package and all messages, feedbacks and other materials sent out to individual patients are different from each other. PHMA is the first project that adopts comprehensive tailoring and if proved effective, it should have important implications for future research, practice and policy-making.

*Trial registration* ISRCTN10999269. July 17, 2020; https://doi.org/10.1186/ISRCTN10999269.

**Supplementary Information:**

The online version contains supplementary material available at 10.1186/s12872-021-01943-5.

## Background

The number of patients with hypertension has reached 1.13 billion worldwide [1]. It has increased by 30.0% since 1990 and is projected to increase to 1.56 billion by 2025 [2]. Hypertension causes heavy disease and economic burden. It is the most important risk factor for stroke, heart disease, renal dysfunction and other major diseases [3] and causes an annual deaths of about 9.4 million (17.8% of the total deaths) globally [4]. Hypertension epidemic and burden in China are equally serious. Total hypertension patients and annual deaths attributable to the disease in the country amounted to 300 and 2.5 million respectively [5, 6]. The nation’s annual direct medical expenses due to cardiovascular diseases was estimated as 130 billion yuan (or 18.4 billion USD), of which 36.6 billion yuan (or 5.2 billion USD) was for hypertension treatment [7].

Human responses to hypertension can be divided into two main areas, i.e., clinical treatment and behavioral intervention. Clinical responses comprise antihypertension medication and detection and treatment of hypertension complications. Behavioral interventions include medication adherence and lifestyle modifications, e.g., healthy diet, physical exercise, alcohol and tobacco containment, stress and insomnia coping, and family engagement [8–12]. However, the effectiveness of existing efforts falls far from expected. Most published interventions demonstrated only marginal to moderate efficacy [13, 14]. According to systematic reviews published by The Lancet in 2019, the treatment and control rate in high-income countries was 60.6% and 36.8% respectively [3]; and 29.9% and 10.3% in low- and middle-income countries [15]. The treatment and control rate in China was 38.3% and 14.5% [16].

Although a variety of reasons are attributable to the low treatment and control rates, lack of adequate sensitivity to the real needs of individual patients may play a key role. Contemporary approaches are mainly population rather than individual oriented [17–19]. Population level initiatives are highly feasible since they use only a single protocol for all individuals but suffer from inherent inability in tailoring interventions to the heterogeneous and changing conditions and contexts of individual residents [20]. Both antihypertension treatment and behavior modifications belong to life-time endeavor needing strong persistence under complex and dynamic contexts. This complexity and long-term dynamics make personalized hypertension management (PHM) inevitable since the chance to find identical hypertension determinant systems from different patients decreases exponentially as the number of its influencing factors multiplied by the number of potential variations in each of the factors at different time points increases.

However, PHM requires: a sustained information mechanism capable of constantly collecting and preserving data about relevant status and trajectory of individual patients; a sensitive planning mechanism capable of identifying personalized needs from the serial and multisource data and designing tailored management accordingly; and an effective delivery mechanism capable of implementing the planned interventions on a patient-by-patient base. These are almost impractical with traditional or mainly manual hypertension management. Due to rapidly advancing computing and communication technologies, more and more hypertension patients are using electronic tonometer, electronic weight scale, smartphone and other mobile devices in monitoring their blood pressure (BP) and related conditions [21–23]. This protocol describes a novel PHM package in Anhui, China (hereafter referred to as PHMA) which takes advantages of these new development and incorporates practical technologies from mobile and telemedicine, cloud computing, and programmed algorithms and models in a synergetic way in tackling the PHM requirements.

## Aim/objectives

The primary goal of this study is to test the efficacy of PHMA. The study hypothesis is that hypertension patients in the intervention arm will, compared to those in the control condition, demonstrate: (a) lower systolic and diastolic BP: (b) higher scores on objective behaviors including self-monitoring, treatment adherence, healthy diet, physical activities, tobacco/alcohol containment, anxiety/insomnia coping, family engagement; and (c) reduced use of medical care due to hypertension and its complications. A second objective of this study is to identify key facilitators, barriers and corresponding strategies in disseminating and implementing PHMA.

## Methods/design

### Intervention ingredients and tailoring

#### Overall framework

As shown in Fig. 1, PHMA aims at preventing and reducing hypertension harms by eight objective behaviors including: (a) attending and responding to project messages/contacts; (b) performing self-monitoring and reporting; (c) modifying unhealthy diet habits or practices; (d) maintaining adequate physical exercise/activities; (e) containing tobacco and alcohol consumption; (f) addressing emotion and sleep problems; (g) using clinical checkups and treatment; and (h) facilitating family engagement. These objective behaviors are promoted through two intervention stages and five intervention measures. More specifically, the intervention for each participating patient starts with an orientation stage followed by a problem-solving stage. The orientation stage aims at equipping the patient with essential knowledge and attitudes about each of the objective behaviors applicable and helping him/her start to practice these behaviors. While the problem-solving stage facilitates the patient to identify and solve problems or barriers encountered in practicing the objective behaviors initiated in the orientation phase. The five intervention measures are: support for self-monitoring (I1), supervised machine communication (I2), daily education or reminder message (I3), weekly blood pressure notification (I4), and quarterly signed feedback (I5). Design of detailed content or procedures of these measures is guided by popular theories or strategies including system synergy [24], health belief model [25], social cognition theory [26], motivational interviewing [27], nudging strategies [28] and computerized tailoring. The following subsections briefly introduce each of the intervention measures.

**Fig. 1 Fig1:**
[figure not shown]
Conceptual framework of personalized management for hypertensive patients

#### Support for self-monitoring (I1)

PHMA provides necessary technical support for participant patients to facilitate their practice of the objective behaviors especially self-monitoring. First, it maintains a cloud database and web-based support system capable of receiving, storing and processing patients’ self-monitored data and allowing them to view their personal records and feedbacks. Second, the project provides each participant patient with an electronic tonometer which: allows the patient to measure point SBP, DBP and pulse at home; sends the results to a cloud data center maintained by the project; and receives and plays voice messages disseminated from the cloud center. Third, the project encourages the participating patients to log onto their personal online accounts to: view their hypertension management profile (Fig. 2) and all the messages, notifications, feedbacks and other IEC (information, education and communication) materials he/she has received in the past; and administer relevant self-monitoring questionnaires (Additional file 2: Appendix 1) as suggested.

**Fig. 2 Fig2:**
[figure not shown]
Example personalized hypertensive management profile

#### Supervised machine communication (I2)

PHMA delivers supervised machine communication (SMC) via telephone at the beginning when the patient enrolls into the project and then at the end of every three months. The communication is conducted mainly by an artificial intelligence (AI) voice processing system according to preset transcripts but the process is supervised by a human professional to handle exceptional machine-patient interactions. SMC comprises baseline and follow-up sessions lasting for about half an hour each time. The baseline SMC introduces PHMA and invites participation in the project, and, if successful, performs a brief yet comprehensive assessment of the patient’s: (a) diagnosis and treatment history; (b) symptoms of hypertension complications; and (c) BP-related lifestyle practices. Each of the follow-up SMC session focuses primarily on the patient’s hypertension management in the past 3-monthes and discusses: status and trends of his/her BP; efforts and progresses made in managing his/her hypertension; difficulties encountered; and plans or suggestions for overcoming the difficulties.

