### Study design and settings

The study adopts a cluster randomized controlled trial (RCT) design involving a total of 60 site communities with 12 in the control arm and 48 in the intervention arm. The control arm maintains existing hypertension case management; while the intervention arms, personalized hypertension management as described above. Project evaluation applies to both arms using the same data collection methods and by same field data collectors. The uneven distribution of site communities between the control and intervention arms was designed to enable detection of potential differences between the control arm and at least four main subgroups with different intervention ingredients within the intervention arm. The analysis and reporting of the trial will strictly follow the CONSORT guidelines [29, 30]. A Trial Steering Committee has been established which holds annual meetings and supervises the trial implementation. For time schedule of the trial please refer to Additional file 1.

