### Selection and randomization of communities

The RCT is implemented in Anhui, an inland province located in eastern China with a population of about 70 million living in 105 cities or counties. Selection of participating sites and patients uses a clustered randomization which proceeds in the following steps: step1 divides Anhui province into north, middle and south regions; step 2 randomly selects 4 cities/counties from each of the three regions; step 3 randomly selects five non-adjacent communities from each of the cities/counties selected; step 4 randomly selects 56 patients diagnosed with hypertension from the communities selected. The five communities selected from each city/county in steps 3 are randomly assigned to the control arm (n = 1) and intervention arm (n = 4). Hypertensive patients aged 18 years or above and capable and willing to participate in the study from the selected communities meet the inclusion criteria. All the randomization is performed by a statistical professional from outside the project team. The study will be blinded to both data collectors and analyst.

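### The invitation to take part sits inside an intervention measure that controls do not receive, so differential enrolment by arm cannot be excluded

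*Protocol article*

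**What the plan says.** All references are to the protocol article.

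- *Overall framework* lists five intervention measures. SMC is the second of them, I2.
- *Supervised machine communication (I2)* times the telephone call "at the beginning when the patient enrolls into the project and then at the end of every three months". Of the first session it says: "The baseline SMC introduces PHMA and invites participation in the project, and, if successful, performs a brief yet comprehensive assessment". Sessions last about half an hour and are run mainly by an AI voice system under human supervision.
- *Study design and settings* states: "The control arm maintains existing hypertension case management". The intervention communities get the personalised package. On assessment it says: "Project evaluation applies to both arms using the same data collection methods and by same field data collectors".
- *Selection and randomization of communities* makes the community the unit of allocation, with one control and four intervention communities per city or county. It samples 56 patients at random and admits adults with hypertension who are "capable and willing to participate in the study". Blinding is stated for data collectors and the analyst. Those who invite patients are not mentioned.
- *Data collection and management* places baseline measurement in the patient's household.

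**The concern.** In a cluster trial, randomising communities does not by itself balance the patients who agree to take part. If patients are asked in a different way in each arm, or by someone who knows the allocation, the enrolled groups can differ before any treatment effect arises. Here the only invitation described is the opening of an intervention measure, and the baseline assessment in that call goes ahead only if the invitation succeeds.

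Patients who accept a mainly machine-run call could differ in motivation, and so in later blood pressure change, from patients who agree to usual care with household visits. Such a difference would enter the primary comparison directly. It would not shrink with more patients, and adjustment for age, sex, education and years since diagnosis would not reliably remove it. If controls were given the same call instead, they would receive part of I2 and the contrast would be diluted.

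**Working it through.** **Setting the sections side by side**

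1. The call is an intervention measure (*Overall framework*).
2. The call carries the invitation, and what follows in it depends on acceptance (*Supervised machine communication (I2)*).
3. Controls keep existing care, so as written they do not receive the call (*Study design and settings*).
4. Only willing patients are included (*Selection and randomization of communities*).

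If the call is the route into the study, it can be confined to intervention communities only when allocation is already known, and controls must be asked some other way. If controls also receive it, step 3 is contradicted. A third arrangement fits the text as well: every sampled patient enters at a common household baseline visit, and only intervention patients then receive the call. The article does not say which applies.

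**Scale of a shift that would matter**

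The plan gives no figure for this point, so there is none to reproduce. The inputs from *Study sample size* are SD of SBP reduction 7.8 mmHg, ICC 0.05, attrition 20% and target difference 5.0 mmHg. The design has 12 control and 48 intervention communities of 56 patients. The plan's 228 per arm is not used.

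- Completers per community: 56 × 0.80 = 44.8, about 45.
- Design effect: 1 + (45 − 1) × 0.05 = 3.2.
- Effective control patients: 12 × 45 / 3.2 = 168.75. Effective intervention patients: 48 × 45 / 3.2 = 675.
- SE = 7.8 × √(1/168.75 + 1/675) = 7.8 × √(1.25/168.75) = 0.67 mmHg.
- Shift equal to the two-sided 5% threshold: 1.96 × 0.671 = 1.32 mmHg.

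With all 56 patients per community, the design effect is 3.75, the SE is 0.65 and the threshold is 1.28 mmHg. With the plan's own design effect of 2.45 and 45 completers, SE = 7.8 × √(2.45 × 1.25/540) = 0.59 and the threshold is 1.15 mmHg.

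False-positive rate if the intervention has no effect and selection alone moves the difference (normal approximation, 45 completers per community; the shifts are assumptions):

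| Assumed shift (mmHg) | Two-sided rejection rate |
|---|---|
| 0 | 5% |
| 0.5 | about 12% |
| 1 | about 32% |
| 2 | about 85% |

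**What refusal could produce such a shift**

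Assume that a share *a* of sampled intervention patients accept, that a larger share *c* of controls accept, and that the extra, more reluctant controls have an SBP change worse by *D*. The shift is then *D* × (*c* − *a*)/*c*. None of these values is in the document.

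| *a*, *c* | *D* = 2 mmHg | *D* = 5 mmHg |
|---|---|---|
| 0.8, 0.9 | 0.22 | 0.56 |
| 0.7, 0.9 | 0.44 | 1.11 |
| 0.6, 0.9 | 0.67 | 1.67 |

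Only the most extreme cell passes 1.3 mmHg. The others are 4% (0.22/5) to 22% (1.11/5) of the 5 mmHg target.

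**The case against.** The strongest reply is that the project and the study need not be the same thing. The abstract presents PHMA as a project built on a package of interventions, *Aim/objectives* says the study tests that package, and under *Support for self-monitoring (I1)* it is the project that supplies the tonometer. On this reading the call invites intervention patients to take up the programme. Refusing it is non-uptake, and a comparison of all sampled patients by assigned arm stays protected.

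Other features also help. Patients are sampled at random, so nobody hand-picks them. Both arms are assessed at home, with the same methods, by collectors who are to be blinded. Patient sampling is listed before the sentence that assigns communities. The time schedule is in an additional file that is not shown, and a full protocol may give the control invitation route. Voice and other channels are meant to suit older and illiterate patients, which argues against strong selection on device skill.

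Much of this stands. A reader might infer that enrolment does differ by arm after randomisation. The document does not establish that, because neither the control route nor the order of consent and allocation is given. The direction of any selection is also not documented.

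The reply does not remove the point. Random sampling comes before consent, so refusal can still differ by arm. Common assessors protect measurement, not who is enrolled. The call is timed to the moment of enrolment, and no sentence puts consent before it or keeps those who decline it in the analysis.

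**Conclusion.** The point holds as a risk that the design text leaves open, not as a demonstrated bias. It rests on what the article states: the invitation is inside I2, I2 is not given to controls, and inclusion depends on willingness. That goes beyond a detail left out of a condensed article, because these statements need reconciling with one another.

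The size of any bias cannot be estimated from the document. The benchmark of about 1.3 mmHg (range 1.15 to 1.32 over the design effects and completion rates tried) depends on the plan's SD of 7.8 mmHg and ICC of 0.05 and on a normal approximation. It says how large a pure selection shift would have to be for its expected value to sit at the 5% threshold. It does not say that such a shift is likely. The change is worth making because it costs little and closes a recognised source of recruitment bias in cluster trials.

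**What to change.** - Take the study invitation out of the SMC.
- In each city or county, have the field data collectors invite, consent and take baseline measurements from the sampled patients in all five communities, using one arm-neutral script, before that county's allocation is disclosed.
- Start SMC only afterwards, in intervention communities.
- State that every consented patient is analysed in the assigned arm whether or not the SMC is accepted.
- Report numbers sampled, invited and consented by arm.

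If a common household entry before the call is already the intention, a sentence saying so, together with the analysis statement, settles the matter.

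The cost is a reordering of steps and one common script, with no added visits. The downside is that allocation is held back until a county's baseline visits are complete. If recruitment has already begun, the order can no longer be changed for those enrolled. In that case, report acceptance and baseline characteristics by arm so that readers can judge whether enrolment differed.

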#### Daily education or reminder message (I3)

PHMA sends short (less than 120 Chinese characters), daily (once a day), and bi-modality (text and voice) messages via: (a) voice electronic tonometer; and (b) WeChat (the most popular social media in China), if the patient is a frequent WeChat user; or (c) mobile phone, if the patient uses mobile phone but are not used to WeChat. Content of the messages differs from patient to patient and from time to time depending on the actual sequence of objective behaviors to be promoted and behavior problems to be addressed. Taking the example shown in Fig. 2, the “intervention focus” during weeks 16–32 was “C” and so all messages send to that specific patient during these weeks centered on “modifying unhealthy diet”. All the messages are purposefully kept short to minimize burden of reading/ listening and a “continued one message every day” strategy is adopted to maintain a consistent bond with the patient and reinforce the objective behavior continuously.

#### Weekly blood pressure notification (I4)

PHMA sends a weekly notification about trends in SBP, DBP, pulse BP and BP control rate in turn for every participating patient. In other words, if a patient receives a short notification about his/her SBP at the end of this week, he/she will receive a notification about DBP, pulse BP and BP control rate at the end of the next one, two and three week(s) respectively. Then these are repeated for every four weeks. Figure 3 uses SBP as an example and illustrates how the content of the notification is generated using the patient’s self-measured blood pressure data.

**Fig. 3 Fig3:**
[figure not shown]
Example flowchart of how blood pressure notification is generated using patient self-measurements

#### Quarterly signed feedback (I5)

PHMA disseminates quarterly feedbacks to each of its participant patients via: (a) paper letter sent via postal service; (b) personal webpage; and (c) WeChat. In the orientation phase, each feedback addresses a specific objective behavior; while in the implementing phase, each feedback addresses a specific barrier to the objective behaviors. All feedbacks comprises five parts: (a) identity and time, to indicate that the feedback is current and addressed to the specific patient named; (b) BP performance, to tell the patient about his/her BP status and trend and indicate that the feedback centers on his/her BP; (c) efforts made recently, to appreciate the patient’s efforts and progresses in the previous 3-months and identify main areas for improvement; (d) actions to take next, to propose feasible actions for the patient to take in the next period; and (e) signatures, to tell the patient that the feedback is produced and checked by authorized professionals and thus useful and reliable. Figure 4 provides an example feedback.

